Quantifying turning performance has traditionally been difficult in clinical settings, but recent advances in wearable sensors have enabled objective, robust, reliable, and sensitive assessments of turning performance in other clinical populations (45, 55–59). This project is designed to transition our previous research findings (8, 9, 21, 45, 55–59) into clinical settings for improved assessments after mTBI by evaluating objective dual-task (DT) turning measures for use as rehabilitative outcomes and as tools for RTD assessments. Therefore, the first goal of this study is to assess diagnostic accuracy—the added value of objective DT turning measures over standard clinical assessments. We hypothesize (a) that objective turning measures, performed in DT contexts, will improve the diagnostic accuracy relative to standard clinical assessments of physical function among people with mTBI and (b) that objective turning measures, performed in DT contexts, will be associated with impairments in International Classification of Functioning, Disability, and Health (ICF) model components, including body functions and structures, activities, and participation domains (60). The second goal of this study is to determine predictive capacity—if objective DT turning measures predict functional performance in civilian and military relevant tasks. We hypothesize that objective turning measures, performed in DT contexts and obtained in the clinic, will predict functional performance in (a) ecologically relevant civilian environments and in (b) ecologically relevant simulated high-demand battle drills. Our third goal in this study is to assess responsiveness to rehabilitation—the responsiveness of objective DT turning measures to standard vestibular rehabilitation in active-duty SMs with residual mTBI-related symptoms. We hypothesize that objective turning measures, performed in DT contexts, will measurably improve over the course of customary rehabilitation for SMs with mTBI-related residual symptoms.

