#### Statistical Analysis

To evaluate the capability of objective, DT turning measures to discriminate between healthy controls and people with mTBI, we will construct receiver operating characteristic (ROC) curves using each objective turning outcome and clinical assessment of activity. The area under the ROC curve (AUC) will be calculated, and AUC confidence intervals will be generated through a bootstrapping procedure. We will compare the AUCs and confidence intervals between each objective turning measure and clinical assessment of activity using tests of equality and a 0.05 significance level with Holm-Bonferroni corrections to adjust for multiple comparisons.

To assess the capacity of DT turning measures to predict performance in civilian or military-relevant tasks, we will use Pearson correlation coefficients and linear regression models. Pearson correlation coefficients will compare the linear relationship between objective turning outcomes and the primary outcome of task completion time during the CAT and throughput during the SUP tasks within participants with mTBI, healthy control participants, and all participants together. To determine how changes in objective turning measures correspond to changes in functional performance, linear regression models will be built for each objective turning measure that was significantly associated with functional performance. The primary outcomes for the civilian and military-relevant tasks will be modeled as the dependent variable. To account for potential differences in performance between civilians and active-duty SMs, a group effect will be included as a covariate. Beta coefficients will be interpreted to identify the relative change in objective turning measures that are associated with changes equal in magnitude to 1 standard deviation of the healthy control participants' performance.

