### Secondary Statistical Analyses

To evaluate if turning outcomes have added value over standard clinical assessments of physical function, base multivariate logistic regression models will be constructed for each clinical assessment of physical function (e.g., FGA, HiMAT). A “base + 1” logistic regression model will be built by adding the objective turning measure with the highest AUC as described above. ROC curves will be constructed for the base and “base + 1” models, and the AUC calculated and compared using likelihood ratio tests. If the AUC from the “base + 1” model is greater than the AUC of the base model, then the process will be repeated iteratively—the outcome measure with the next largest univariate AUC will be added to the “base + 1” logistic regression model to create a “base + *n*” model until the addition of outcomes does not significantly change the AUC.

To evaluate if objective turning measures will be associated with impairments in ICF model components, including body functions and structures, activities, and participation domains, Pearson and Spearman correlation coefficients will be implemented separately within healthy civilian control participants, healthy active-duty control participants, and civilians with mTBI. Linear regression models with ICF impairments (Table 2) as dependent outcomes and main effects of objective turning outcomes, group, and the group ^*^ turning outcome interaction will assess whether the association between objective turning outcomes and ICF function varies by group through the interaction term. A 0.05 significance level will be used with stepwise Holm-Bonferroni corrections to adjust for multiple comparisons.

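### The base + 1 test of added value treats the best of many turning measures, chosen by AUC in the same participants, as if it had been fixed in advance

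*Protocol article*

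**What the plan says.** The main Statistical Analysis section builds ROC curves "using each objective turning outcome and clinical assessment of activity", with bootstrap confidence intervals for the AUCs and Holm-Bonferroni correction of the head-to-head comparisons.

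Secondary Statistical Analyses then takes up added value. A logistic base model is fitted for each clinical assessment of physical function, with the FGA and HiMAT as examples. The base + 1 model is formed by "adding the objective turning measure with the highest AUC as described above", a reference back to those ROC results. The models have "the AUC calculated and compared using likelihood ratio tests". If the new AUC "is greater than the AUC of the base model, then the process will be repeated iteratively": "the outcome measure with the next largest univariate AUC will be added" to form base + n, "until the addition of outcomes does not significantly change the AUC".

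The Introduction describes the first goal as "the added value of objective DT turning measures over standard clinical assessments".

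**The concern.** Ranking, fitting and testing all use one set of participants, and the term tested is the one that looked best in that set. Judging its LRT against the usual chi-square cut-off treats the term as if no search had taken place.

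Neither safeguard in the article reaches this step. The bootstrap serves the AUC confidence intervals only. The Holm-Bonferroni sentence in the secondary section closes the paragraph on ICF associations. Even if it extended to base + n, it would count the tests carried out, not the candidates searched.

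Two consequences follow: added value may be declared too often, and the reported rise in AUC is an in-sample figure that will shrink in new patients. This matters because the Discussion links improvement over standard assessments, together with the other two goals, to rapid adoption in return-to-duty decisions.

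**Working it through.** **The plan's own figure.** The article states no error rate for base + n. Its power figure for the group comparison does reproduce: 50 per group, effect 0.65 × 1.20 = 0.78, two-sided alpha 0.01. The noncentrality is 0.78 × √(50/2) = 3.90 and the normal approximation gives Φ(3.90 − 2.576) = 90.7%; the noncentral t gives 89.6%. The article says 90%.

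**Number of candidates.** Table 1 lists six objective turning outcomes. Four are starred for both mean and SD, so there are 4 × 2 + 2 = 10 per task condition. Three tasks give 10 × 3 = 30 dual-task candidates.

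**Upper bound.** If the candidates were independent, the chance that at least one passes at 5% would be 1 − 0.95^10 = 40% for 10 and 1 − 0.95^30 = 79% for 30. Correlation lowers this, so the step was simulated.

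**Simulation of the first step.**
- From the article: 50 mTBI versus 50 civilian controls; the candidate with the largest univariate AUC is added.
- Assumed: the test level (1-df LRT at 0.05, since the article states none for this step), one clinical score separating the groups by 0.8 SD, normal candidates, and their mutual correlation.
- Two nulls: (a) candidates unrelated to group and to the clinical score; (b) candidates that track the clinical score at about 0.5, and so separate the groups, but add nothing beyond it.

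False declarations of added value (ranges are over repeated runs, some with a base separation of 0.55 SD under null (b)):

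| Null | Candidates | Correlation 0.5 | Correlation 0.8 |
|---|---|---|---|
| (a) pure noise | 10 | 26–27% | 16–17% |
| (a) pure noise | 30 | 41–43% | 21–24% |
| (b) tracks the score | 10 | 13–15% | about 10% |
| (b) tracks the score | 30 | 24–27% | 13–17% |

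For null (b) the correlation is the residual one, given the clinical score. At 0.9 with 30 candidates the rate is 15–16% under (a) and 9–12% under (b). With a base separation of 0.55 SD, null (a) with 30 candidates at 0.5 gives 47%.

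**Isolating the cause.**
- One measure fixed in advance: 4–6%, so the LRT itself is sound.
- Best measure selected, but tested at 0.05/m for m candidates: 1–6%.
- Best measure selected, tested at 0.05/3 as if only three base models needed correction: 5–19%.
- 50 versus 90, in case the active-duty controls are included: 24–26%.

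**AUC gain.** With selection and correlated candidates the in-sample AUC rose in 76–97% of null runs, on average by 0.01 to 0.03. A single unselected noise measure raised it in 72–75%.

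**The case against.** Several points on the other side stand.

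- *The LRT.* A reader might infer that the LRT is the wrong test and drives the false positives. It does not: for nested logistic models it is a valid test of the added coefficient. The fault is the description of it as a comparison of AUCs. An ordinary paired AUC test (DeLong) would be no remedy, since it rejects in only 0–2% of most of these null runs.
- *The size.* A reader might quote about half of trials or more. That needs pure-noise candidates with moderate correlation, or 60 candidates with single-task measures counted. The preliminary data in Sample Size show peak lumbar velocity separating the groups, so null (b) is the more relevant one. Hypothesis (a) and the ROC analysis are framed around dual-task measures, so 60 is poorly supported. The lumbar, trunk and head speeds may also be highly correlated, which lowers the rate.
- *The stopping rule.* A reader might see two contradictory rules. Taken literally, a larger AUC starts the iteration and significance ends it, and the first may be shorthand for a significant increase. The conflict is minor, although a larger in-sample AUC is no real hurdle.
- *The role of the step.* A reader might call this the only test of hypothesis (a). The main section also compares turning with clinical measures, with correction, and base + n is labelled secondary.
- *The unseen plan.* The lack of internal validation in an article is not itself a fault. The point rests on the selection and testing rule that the article does state.

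None of this removes the selection effect, which remains at roughly two to five times nominal under null (b).

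**Conclusion.** The point holds as a should-fix on a secondary analysis that bears directly on the added-value goal. As written, the first step declares added value falsely in roughly 10% to 45% of null trials instead of 5%. For 30 dual-task candidates the figures are about 13–27% when turning tracks the clinical score and about 20–45% when it is noise. The apparent AUC gain is biased upwards in either case.

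The direction follows from the stated procedure. The size depends on the number of candidates, their correlation and the strength of the base score. The article gives neither the correlations nor the base separation, so the result is a range and not a single figure.

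**What to change.** 1. Name one base + 1 variable in advance from the declared primary outcome, dual-task peak lumbar turning speed. Naming the outcome alone is not enough: three tasks, each with mean and SD, leave 3 × 2 = 6 candidates, and picking the best of those still gives about 10–21% false positives. State one task and either mean or SD. Test it by LRT, described as a test of model fit and not of AUC.
2. Label the data-driven base + n search exploratory. Bootstrap the whole procedure (ranking, selection, stopping and fitting) and report the optimism-corrected AUC gain with its interval.
3. State one rule for continuing and stopping, the LRT for the added term, in place of the condition that the AUC is larger.

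The cost is analysis code and wording. No new data are needed; the reported AUC gains will be smaller.

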### Phase 1: Diagnostic Accuracy and Predictive Capacity of Turning Measures

#### Participants

Phase 1 will include approximately 50 civilians with persistent symptoms from mTBI, 50 civilian healthy controls, and 40 active-duty SM healthy controls. Three non-military sites (OHSU, UU, CKRC) will test civilians. A fourth military site (FSH) will enroll and test 40 active-duty SM healthy controls across a range of military experience and ability levels.

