To determine clinically viable measures of turning based on clinometric properties, we will calculate the repeatability and minimum detectable difference using a Bland-Altman framework on the subset of participants who complete two blocks of turning tasks (80, 81). Linear mixed models will be fit for each objective outcome measure and task combination, with site location included as a covariate. Random intercepts will be fit for each participant to control for repeated measurements. Repeatability and minimum detectable change will be assessed using the within-subject error term for each outcome measure. Minimum detectable change will be calculated as $1.96^{*}\sqrt{2}$ times the within-subject error of the civilian control, military control, and civilian mTBI groups separately, as well as all groups combined. Differences across sites will be assessed using the standard error of effect of site location. Intraclass correlation coefficients will assess the absolute agreement and consistency of the outcomes across difference testing blocks. Outcomes with ICCs >0.7 will be identified as having good agreement and consistency for clinical implementation. Bias and learning effects will be considered by directly investigating the mean and median difference between blocks using a Bland-Altman framework (80, 81).

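### Site differences are to be assessed by the standard error of the site effect, which measures precision and does not change with the size of the difference

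*Protocol article*

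**What the plan says.** The passage is in the Protocol article, Secondary Statistical Analyses, in the paragraph on repeatability and minimum detectable change. The data are those collected "on the subset of participants who complete two blocks of turning tasks". The model is described as follows: "Linear mixed models will be fit for each objective outcome measure and task combination, with site location included as a covariate". The only random effect named is a participant intercept: "Random intercepts will be fit for each participant to control for repeated measurements". The rule for site is then a single sentence: "Differences across sites will be assessed using the standard error of effect of site location". It names no site estimate, interval, test or between-site variance.

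The same paragraph treats the comparison of the two blocks differently: "Bias and learning effects will be considered by directly investigating the mean and median difference between blocks".

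The Phase 1 Participants section gives three civilian sites and one military site: "A fourth military site (FSH) will enroll and test 40 active-duty SM healthy controls across a range of military experience and ability levels". No other section gives a different rule for judging site differences.

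**The concern.** A standard error says how precisely a difference is estimated. It does not say how large the difference is. Two sites that agree perfectly and two that are far apart give the same standard error if they have the same numbers and the same spread. A site with few retested participants has a large standard error with no true shift, and a well-filled site has a small one despite a real shift.

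At stake is the article's one stated check on whether the turning measures read alike at different sites. If the rule is followed literally, a site shift could be present in the data and the reported statistic would not reveal it.

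**Working it through.** The article gives no figure on this point, so there is none to reproduce. The check asks whether the named statistic responds to a site difference.

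**Inputs from the article.** Site is a fixed covariate, there is a random intercept per participant, and each retested participant has two blocks.

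**Assumed inputs.** The article gives none of these: between-subject SD sb = 1.0, within-subject SD sw = 0.5, and 5 to 30 retested participants per site. For scale, retesting all 100 civilians at three equal sites would give about 33 per site, and the article retests only a subset.

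**Formula.** With two blocks per participant, the participant mean has variance sb² + sw²/2. For two sites A and B:

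SE(A − B) = √[(sb² + sw²/2) × (1/nA + 1/nB)]

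The true difference between A and B does not appear. A shift at one site is absorbed by that site's coefficient. The residuals, the variance components and the standard error are left unchanged.

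**Step 1: vary the numbers, with no site difference.** Here sb² + sw²/2 = 1 + 0.125 = 1.125.

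| Per site | Calculation | SE |
|---|---|---|
| 5 | √(1.125 × 2/5) | 0.67 |
| 10 | √(1.125 × 2/10) | 0.47 |
| 15 | √(1.125 × 2/15) | 0.39 |
| 30 | √(1.125 × 2/30) | 0.27 |

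The statistic more than halves although the sites are identical throughout.

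**Step 2: vary the true difference, with 15 per site.** This used 200 simulated datasets per setting and three sites, one of them shifted. The analysis was on participant means, which is equivalent to the mixed model when every participant has both blocks.

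| True shift (SD) | Mean SE | Mean estimate | Share with p < 0.05 |
|---|---|---|---|
| 0 | 0.385 | 0.02 | 4.5% |
| 0.5 | 0.385 | 0.49 | 23.5% |
| 1 | 0.381 | 1.01 | 74% |
| 2 | 0.381 | 2.03 | 100% |
| 3 | 0.382 | 2.96 | 100% |

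The formula gives 0.387. The small movements in the SE column are simulation noise.

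**Step 3: one dataset, mixed model fitted directly, shift added to one site.** The interval is estimate ± 1.96 × SE, and 1.96 × 0.3829 = 0.75.

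| Shift added | SE | Estimate | 95% CI | p |
|---|---|---|---|---|
| 0 | 0.3829 | 0.03 | −0.72 to 0.78 | 0.93 |
| 1 | 0.3829 | 1.03 | 0.28 to 1.78 | 0.007 |
| 3 | 0.3829 | 3.03 | 2.28 to 3.78 | <0.001 |

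The standard error is identical to four decimals in all three cases. The estimate and its interval, from the same fit, tell them apart.

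**The case against.** The best defence is that the sentence is shorthand. A model with a site covariate returns an estimate together with its standard error, and any Wald test or confidence interval uses that standard error. In a condensed article, the choice of test for a secondary covariate can be left to an analysis plan. This reading is plausible and may be what was meant. It does not remove the point, because the text fixes a specific criterion and that criterion leaves the estimate out. Elsewhere in the same section the authors name their inference, and the same paragraph judges block differences by the differences themselves. If shorthand was intended, the sentence still needs the same correction.

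A second defence is that the SD of a random site effect was meant, which would measure spread between sites. That conflicts with the model described, where site enters "with site location included as a covariate" and random intercepts belong to participants only.

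The objection is right about the limits. Minimum detectable change comes from the within-subject error. Clinical agreement is judged by the intraclass correlation. The ranking under Refinement of Tasks and Outcomes for Future Clinical Use uses the AUC, two correlations and the ratio of rehabilitation effect to minimum detectable change. The site standard error enters none of these.

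**Conclusion.** The point holds as a defect in a stated rule for a secondary analysis. With site as a fixed covariate, the standard error carries no information on how far apart the sites are, and so the check as written cannot show whether they differ. That follows from the form of the model. The numerical standard errors depend on the assumed SDs and subset sizes, and would change with other values.

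Three stronger conclusions that a reader might draw are not supported:

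- **That the plan would flag the site with the fewest retested participants.** The article attaches no flag, threshold or action to the statistic.
- **That the generalizability claim fails.** The Discussion rests that claim on sample size, the use of several sites and the inclusion of both populations. It does not cite this check.
- **That the minimum detectable change or the final choice of task and outcome is compromised.** Neither uses the site standard error.

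The effect is confined to the site comparison. The correction is worth making because the rule as stated does not do its job.

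**What to change.** Replace the sentence so that site differences are assessed by the site-effect estimates with 95% confidence intervals from the mixed model already planned. A joint test of site may be added. The interval should carry the interpretation: under the assumptions above with 15 per site, a single-contrast test at 0.05 detected a 0.5 SD shift in only 23.5% of simulated datasets, so a non-significant result would not show that sites agree.

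Make the comparison among the three civilian sites. In Phase 1, Fort Sam Houston tests only active-duty controls and the other three sites test civilians, so its site effect cannot be separated from service status. A between-site SD is an optional extra and would be poorly estimated from three sites.

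The cost is one sentence. It needs no new data and no new model.

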## Methods/Design

This study has two phases: for Phase 1, participants will be recruited from the general civilian populations surrounding three sites [Oregon Health & Science University (OHSU), University of Utah (UU), Courage Kenny Research Center (CKRC)] and active-duty SMs at one site [Fort Sam Houston (FSH)] to address the first two goals of the study (diagnostic accuracy and predictive capacity). For Phase 2, participants will be recruited from active-duty SMs referred to military medical treatment facilities (Evans Army Community Hospital and Madigan Army Medical Center) for physical therapy following mTBI to address the third goal of the study (responsiveness to rehabilitation). This study has been registered on ClinicalTrials.gov (NCT03892291).

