#### Inclusion and Exclusion Criteria

Participants may be active duty (at FSH), veterans, or nonveterans and must (1) have a diagnosis of mTBI based on Veterans Affairs/Department of Defense (VA/DoD) criteria (61, 62), (2) be between 18 and 50 years old, and (3) be outside of the acute stage (>3 weeks postconcussion) according to the VA/DoD clinical practice guidelines (63) but within 3 years of their most recent mTBI and still reporting symptoms. Control participants must have no history of mTBI or be more than 7 years removed from their most recent mTBI and no reported residual symptoms. All participants must (1) not have had or currently have any other injury, medical, or neurological illness that could potentially explain balance deficits (e.g., central or peripheral nervous system disease, stroke, greater than mild TBI, lower extremity amputation, recent (<6 months) lower extremity or spine orthopedic injury requiring a profile); (2) meet criteria for moderate to severe substance-use disorder within the past month, as defined by *Diagnostic and Statistical Manual of Mental Disorders, Fifth Edition* (64); (3) display behavior that would significantly interfere with validity of data collection or safety during the study; (4) be in significant pain during the evaluation (7/10 by patient subjective report); (5) be a pregnant female (balance considerations); or (6) be unable to communicate in English.

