To determine whether healthy active-duty SMs perform turning tasks differently than healthy civilians, we will fit linear regression models for each turning outcome with main effects of group (active-duty SMs vs. civilians) and adjusted for age, body mass index, and other potential covariates. Inferences will be made using a significance level of 0.05 and a Holm-Bonferroni adjustment for multiple comparisons. If we find outcomes significantly differ between active-duty populations and control populations, we can conclude that population-specific normative values are needed. Given the large sample size of active-duty SMs and controls, we will then separate active-duty and civilian control groups for future analyses using those outcomes with significant differences between active-duty and civilian control participants. If we fail to find differences between active-duty and civilian control groups, it suggests performance does not vary by service status, and normative means, standard deviations, and minimum detectable changes will be calculated by combining data from all healthy control participants. We will also compare the distributions of performance using interval estimators to determine the extent to which the range of performance overlaps between active-duty SMs and civilians.

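### Among Phase 1 healthy controls, service status and test site coincide, so the active-duty versus civilian comparison cannot support either stated conclusion about norms

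*Protocol article*

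**What the plan says.** **Who is tested where.** Methods/Design and the Phase 1 Participants section of the protocol article assign the groups to different sites. On civilians: "Three non-military sites (OHSU, UU, CKRC) will test civilians". On service members: "A fourth military site (FSH) will enroll and test 40 active-duty SM healthy controls across a range of military experience and ability levels". The eligibility section agrees: "Participants may be active duty (at FSH), veterans, or nonveterans". The healthy control groups are "50 civilian healthy controls, and 40 active-duty SM healthy controls".

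**The model.** For each turning outcome, the Secondary Statistical Analyses plan a linear regression with "main effects of group (active-duty SMs vs. civilians) and adjusted for age, body mass index, and other potential covariates". The level is 0.05 with a Holm-Bonferroni adjustment. Site is not named as a term.

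**The rule.** A significant result leads to this: "If we find outcomes significantly differ between active-duty populations and control populations, we can conclude that population-specific normative values are needed". The two control groups are then kept apart in later analyses of those outcomes. A non-significant result is read as a sign that service status makes no difference, and normative means, standard deviations and minimum detectable changes are computed from all controls together. The range of performance in the two groups is also compared with interval estimators.

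**Site elsewhere.** The repeatability analysis includes site as a covariate and adds: "Differences across sites will be assessed using the standard error of effect of site location". The article does not mention that service status and site coincide among the controls.

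**The concern.** The comparison is meant to show whether service members turn differently from civilians. As designed, it compares one site with three others. Whatever is particular to testing at FSH enters the group coefficient together with any effect of military service, and its standard error reflects only variation between people.

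Both branches of the rule are exposed. A site difference alone can produce the conclusion that separate military norms are needed. A site difference opposed to a true service difference can cancel it and lead to pooling. The analysis is secondary, but it decides whether controls are split or combined later, and the Discussion uses it to support population-adjusted normative ranges.

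**Working it through.** **Inputs from the article.** 50 civilian healthy controls at three sites; 40 active-duty healthy controls at one other site; level 0.05 (taken as two-sided). The article gives no power or error figure for this comparison, so there is no stated figure to reproduce.

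**Assumed inputs.** No between-site SD is given. Let s be the between-site SD in units of the within-site SD, and take 0.1, 0.2 and 0.3. The three civilian sites are taken as equal in size.

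**Step 1: can the model separate site from service?** A design matrix for the 90 controls with an intercept, a group indicator and three site indicators has 5 columns but rank 4. The FSH indicator is the group indicator. A fixed site term cannot be estimated alongside group, and age, body mass index or any other covariate leaves this unchanged.

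**Step 2: false positives with no service effect.**
- Variance of the mean difference that the planned test recognises: 1/40 + 1/50 = 0.045.
- Variance with site effects: 0.045 + s²(1 + 1/3), from one military site and the mean of three civilian sites.
- Rejection rate: 2[1 − Φ(z·√(0.045 / true variance))], with z = 1.96 for a single 5% test and z = 2.64 for an assumed first Holm step of 0.05/6 = 0.0083.

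| s (assumed) | True variance | Single 5% test | Step of 0.05/6 |
|---|---|---|---|
| 0.1 | 0.0583 | 8.5% | 2.1% |
| 0.2 | 0.0983 | 18.5% | 7.4% |
| 0.3 | 0.1650 | 30.6% | 16.8% |

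A simulation of the t-test (40,000 runs; civilian sites of 17, 17 and 16; FSH 40) agrees. Site shares of total variance of 0.01, 0.05 and 0.10, which correspond to s of about 0.10, 0.23 and 0.33, gave 8.7%, 20.9% and 33.2% at the 5% level.

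**Step 3: masking.** By the noncentral t distribution with 50 and 40 controls, a net difference of 0.6 SD is detected with probability 80% at the 5% level. Suppose a true service difference of 0.6 SD is met by an opposing FSH shift of 0.3 SD (both assumed). The net difference is 0.6 − 0.3 = 0.3 SD, which is detected with probability 29%. Pooling would then be the usual outcome despite a true difference.

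**Step 4: does a random site effect rescue the comparison?** With site as random, the contrast rests on 4 sites, one against three, with about 4 − 2 = 2 degrees of freedom. The critical t is 4.30, against 1.99 with 88 degrees of freedom. The uncertainty is then stated more fairly, but FSH's own site effect still cannot be estimated.

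**The case against.** The strongest reply is that the damage depends on site effects that nobody has shown. The turning tasks and sensors are common to all sites, which may keep such effects small, and no section says that premises, testers or equipment differ. The repeatability section plans to assess site differences. A reader might infer that it expects them, but it does not say so. This part of the objection stands: the article does not support a claim that the error rate is in fact far above nominal. At s = 0.1 the single-test rate is 8.5%, and Holm-Bonferroni lowers all the absolute rates. It does not remove the inflation, since 2.1%, 7.4% and 16.8% all exceed the 0.83% of the assumed step.

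A reader might also infer that FSH is the only site testing service members. That is too broad. Phase 2 recruits 40 active-duty members at two other military facilities, who perform the same tasks at baseline. It is tempting to treat those data as the cure, but they are all symptomatic patients referred for physical therapy and add no healthy service member. Within the military sites, injury status is itself aligned with site: FSH contributes healthy members only, and the other two contribute members with mTBI only. Using them to estimate a service effect requires the mTBI effect to be equal in referred service members and in civilians.

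Finally, the analysis is secondary, the Discussion words its conclusion more cautiously than the analysis section, and overlap of the distributions is also reported. This limits the consequences. But the overlap comparison has the same confounding, and the decision rule is stated without qualification.

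**Conclusion.** The confounding is certain and complete for Phase 1 healthy controls. It follows from the recruitment plan and needs no assumption. Neither stated inference is supported: a significant difference does not by itself show that population-specific norms are needed, and a non-significant one does not show that performance is unrelated to service status.

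The size is conditional. The single-test false-positive rates of about 8.5%, 18.5% and 31% rest on assumed between-site SDs of 0.1, 0.2 and 0.3, equal civilian sites and no service effect. With no site effect the planned test keeps its level. The documents do not say which case applies, and the three civilian sites can show how much civilian sites vary but cannot reveal FSH's own effect. This is a flaw in a stated inference rule rather than a detail left to the analysis plan, because no added fixed covariate could repair it.

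**What to change.** In the active-duty versus civilian part of the Secondary Statistical Analyses:

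1. Label the contrast as FSH active-duty controls versus civilian-site controls.
2. Report it with its interval beside the estimated spread among the three civilian sites, as context and not as a test threshold.
3. Replace both conclusions (separate norms needed; performance unrelated to service status) with a statement that site and service cannot be separated in this design, so that separate or pooled norms are provisional.
4. Optionally, as a sensitivity analysis only, fit a random-site model that adds the Phase 2 baseline data and adjusts for mTBI status. State its assumption that the mTBI effect is equal in referred service members and civilians.

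The required items cost a change of wording and one extra summary. The price is a weaker claim about service status. A stronger claim would need a design change, such as civilian controls at FSH or healthy service members at another site.
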